## Abstract

**Background:**

The workplace has been identified as a key determinant of health status. There is evidence of innumerable health problems among employees, particularly healthcare workers. Against this background, a holistic-systemic approach together with a good theoretical framework is required to reflect on this issue, and to support the design of effective interventions to promote the health and wellbeing of the given population. The present study aims to evaluate the effectiveness of an educational intervention in improving resilience, social capital, psychological wellbeing, and health-promoting lifestyle in healthcare workers, utilizing the Social Cognitive Theory integrated into the PRECEDE-PROCEED model.

**Methods:**

This randomized controlled trial will be performed on a large sample of the employees working in two healthcare centers in the city of Shiraz, Iran. The study will proceed with the healthcare workers of one city being given the educational intervention and the healthcare workers of the other city serving as a control group. Using a census method, all healthcare workers in the two cities will be informed of the trial and its purpose, and then invitations to join the study will be issued. The minimum sample size required has been calculated as 66 individuals in each healthcare centers. Recruitment to the trial will by systematic random sampling of eligible employees who submit an expression of interest in joining the trial, and subsequently give informed consent. Data will be collected through a self-administered survey instrument at three stages: at baseline, and both immediately and three months after the intervention. The experimental group members should participate in at least eight of the ten weekly educational sessions of the intervention and complete the surveys in the three stages. There is no educational intervention for the control group, and they simply experience some routine programs, and complete the surveys at the same three timepoints.

**Discussion:**

The findings will provide evidence for the possible effectiveness of a theory-based educational intervention to improve resilience, social capital, psychological wellbeing, and health-promoting lifestyle among healthcare workers. If the educational intervention is found to be effective, then its protocol will be exploited in other organizations to boost resilience.

*Trial registration* IRCT20220509054790N1.

## Background

The workplace has been identified as being among the main determinants of health [1]. From this perspective, a healthy workplace has the potential to bring many positive changes in employees, such as good health, higher levels of job satisfaction, and reduced absenteeism, which all contribute to improved quality of work life, and better productivity [2, 3]. Nevertheless, there is evidence of high levels of innumerable health problems among employees, particularly, healthcare workers (HCW). In particular, large sections of the working population exhibit poor mental health with evidence that excessive anxiety, emotional exhaustion, and psychological stress are rife [4]. Regarding HCW, exposure to daily crises—especially during the ongoing COVID-19 pandemic—has given rise to heavy burdens being imposed on this workforce, and high incidence rates of psychological disorders among them [5]. Any decrease in health status can reduce the quality of life (QoL) of HCW, and subsequently influence their life satisfaction [6]. These problems are harmful to the professional HCW, and also, via a reduction in their productivity in the workplace, the people they look after, and the wider society [7–9]. It follows from this that there is a business case for intervention, as well as moral and ethical reasons. There is evidence that the highest levels of sickness absence are in HCW [10]. The costs associated with sickness absence and reduced productivity are an important issue for employers, and a driver for providing resources for interventions [10–12]. Thus, a focus on HCW when designing novel, expensive interventions to improve quality of life in the working population is an effective approach.

A wide variety of factors can shape employees’ mental health. At the individual level, studies have established that many HCW might lack resilience and stress management skills [13]. At the interpersonal level, no support from coworkers or family members might contribute to the emergence and exacerbation of the problems [14]. The quality of communications between managers and employees, along with perceived justice, have also been reported to shape mental health in employees at the organizational level [15]. It follows from this that multiple interventions are often required for multi-causal health problems [16]. Therefore, the effectiveness of mental health-promoting interventions in the workplace depends on adopting a holistic-systematic and evidence-based approach together with a good theoretical framework to promote the health and wellbeing of the given population. Characterized by having an ecological-holistic approach, the PRECEDE-PROCEED model provides a suitable roadmap for this purpose [17]. This PRECEDE-PROCEED model represents a process to change behavior, and a structure to systematically apply theories and concepts in order to plan and evaluate the success rate of educational health promotion programs regarding behavior change [18–22]. The PRECEDE-PROCEED model has been successfully used in several workplace-based health promotion programs [17] which also strongly supports its suitability for the problem being addressed in the proposed research. As a systematic planning framework, it comprises eight phases for analyzing a problem, designing an intervention, and finally evaluating a program [21]. In line with all health-promotion interventions, promoting the QoL is the ultimate goal of the PRECEDE-PROCEED model [22]. The eight phases of the model are listed in column 1 of Table 1.

In the present study, the groundwork for the evidence-based targeted intervention measures that will be implemented and evaluated was provided by a review of the literature to assess the social and epidemiological background of similar HCW populations. This approach implemented the first three phases of the PRECEDE-PROCEED model and was essential to achieve a logical framework for planning the health-promoting intervention and identifying its components. The social, epidemiological, behavioral, and environmental assessment provided by the literature review found evidence that the mental health and QoL of HCW was negatively by their work, particularly since the outbreak of the COVID-19 pandemic [23, 24]. It also confirmed that QoL can be affected by one’s health conditions [25–27]. Psychological wellbeing (PWB) is accordingly one of the determinants of the QoL among employees [28], and it is strongly influenced by one’s psychosocial environment and behavior. Here, wellbeing refers to a concept that defines the quality of work life, as a main determinant of productivity in individuals, organizations, and society [29]. People with low wellbeing may thus evaluate events and situations in their lives as adverse ones, and undergo negative emotions, e.g., anxiety, depression, and anger [30].

With respect to environmental determinants of health, evidence suggests that the conditions related to the psychosocial environment affect employee health more than the physical setting characteristics [31]. Social capital is one of the major components of the psychosocial environment at work [32]. The concept of social capital in the workplace represents the attitudes and values ​​among members, mutual action, respect, and trust between coworkers, collective action, contribution to networks, and trust in honesty among managers at work [33]. The workplace is correspondingly an essential source of social capital for many people, which provides mutual support and gives meaning to life [34]. Evidence indicates that social capital is significantly correlated with health outcomes, organizational outcomes, and a health-promoting lifestyle (HPL) in employees [35]. In the dimension of organizational outcomes, social capital can have a greater impact on job success, knowledge sharing, increased communication, and improved chances of organizational survival [36, 37]. Social capital also seems to be associated within the HPL dimension. If being deprived of healthy lifestyle can result in depression, absenteeism, and low productivity at work, then keeping employees healthy and productive is crucial for boosting productivity at the organizational level [38]. Likewise, there are reciprocal relationships between social capital, PWB, and resilience. Resilience denotes a set of protective strategies used by individuals in situations they once encountered with difficulty or deprivation. Such strategies change the way a person reacts to difficulties, and they often integrate both internal and external factors in a positive direction, with favorable outcomes, such as maintaining or returning to health. Demonstrating resilience also leads to positive mental health or prevention of some negative consequences [39]. Recent viewpoints consider resilience as a capacity that can be consciously developed through learning processes [40–42]. Similarly, it has been argued that resilience training can improve mental health and wellbeing outcomes for workers [43]. Resilience accordingly plays a leading role in helping employees to successfully reach adaptation, handle emotional pressure, develop effective coping strategies, and improve their wellbeing [39]. Accordingly, the main goals of developing social capital, PWB, and resilience in the workplace bear a resemblance. In other words, one of the hypotheses arising from such facts is that the elevation in resilience skills improves social capital, and both promote PWB. In such a context, a HPL will be more encouraged by bolstering the psychological-social atmosphere in the workplace [30, 44].

The third phase of the PRECEDE-PROCEED model is an educational and ecological assessment, wherein the determinants of behavior and environment are typically examined in three categories: predisposing, reinforcing, and enabling factors. Here, predisposing factors include knowledge, attitudes, self-efficacy, outcome expectations, and outcome values; reinforcing factors are perceived social or organizational support, and enabling factors consist of having access to and support of resources and personal skills [22–24]. In different phases of applying the PRECEDE-PROCEED model, especially in the third phase, the specific theories of behavior change related to the research problem and setting can be used [20, 45], which help in augmenting the internal validity of the study. In light of this, the Social Cognitive Theory (SCT) is suitable for the analysis of the problem in the PRECEDE-PROCEED model. This theory can explain human behavior in terms of having three-way causality (individual, environmental, and behavioral) [46, 47], whose interactions can produce behavior change [48, 49].

The fourth phase of the PRECEDE-PROCEED model includes a review of educational programs, policies, and procedures within an organization, and ultimately the intervention program is developed. During the fifth phase, the proposed intervention program is implemented among employees, then in phases six to eight comprise process, impact, and outcome evaluations [21, 22, 24, 50].

To date, interventions to improve resilience towards better health outcomes have lacked a longitudinal element, good outcome measures, and comprise other design issues [51]. Similarly, despite strong assertions that improving social capital can improve health, there is a dearth of intervention studies to examine these claims [52]. In general, it seems that the PRECEDE-PROCEED model integrated into the three SCT factors (individual, environmental, and behavioral) can be exploited as a suitable theoretical framework for the design and evaluation of mental health-promoting interventions among HCW in a longitudinal RCT. Therefore, the aim of this study is to determine the effects of an evidence-based educational program on resilience, social capital, PWB, and HPL in HCW, using the SCT integrated into the PRECEDE-PROCEED model.

### Research hypotheses

The change mean scores of the study constructs (viz. resilience, social capital, PWB, HPL, and resilience) among HCW in the experimental and the control groups are different after the intervention is completed.There is a significant correlation between resilience and social capital, resilience and PWB, and resilience and HPL in both experimental and control groups.There is a significant correlation between the constructs of the SCT and the variables of resilience, social capital, PWB, and HPL.

## Methods

### Study design, setting and participants

This quasi-experimental study is a non-blinded randomized controlled trial (RCT) (Code: IRCT20220509054790N1) with assessments at baseline, immediately after the intervention, and three months after the intervention. This study was approved by the Ethics Committee in Medical Research affiliated to Shiraz University of Medical Sciences, Shiraz, Iran.

Recruitment will be from two large healthcare centers in the northern and southern parts of the city of Shiraz, in southern Iran (namely, Wal-fajr and Enghelab). Permission to undertake the study in these two healthcare centers was sought as they are comparable in their cultural and socio-economic characteristics. This method has previously been used as a means of preventing information exchange between the participants in the experimental and control groups [53]. The two healthcare centers will be randomly assigned to intervention and control settings following recruitment. Using the MedCalc software and the following formula:$$n \ge \frac{{(Z_{{1 - {\raise0.5ex\hbox{$\scriptstyle a$} \kern-0.1em/\kern-0.15em \lower0.25ex\hbox{$\scriptstyle 2$}}}} + Z_{{1 - \beta }} )\left( {\sigma _{1}^{2} + \sigma _{2}^{2} /r} \right)}}{{(\mu _{1} - \mu _{2} )^{2} }}$$

The sample size is estimated to be 66 participants in each group. Considering the 5% loss of observations, the final sample size will be determined to be 69 in each group.

The study has been advertised in the two healthcare centers, and information about the study distributed to all HCW. Inclusion criteria are being employed at the healthcare center, aged 25–60 years, and no self-reported history of severe physical or mental illness. (This will also be checked again at the community survey stage). Exclusion criteria are severe physical or mental illness, not giving informed consent, reluctance to continue the study/not participating in either intervention and/or surveys. For sampling, first, an alphabetical list of the names of all HCW in both centers is prepared. Thenceforth, the samples will be selected in a randomized manner. If a person is not eligible, or does not give written informed consent, then they will be replaced with the next one available on the list will be replaced. Baseline data will then be collected from all participants. There are no incentives for participating in the research, but also no costs because data collection will be during working time. All participants who complete the study will be given a certificate of participation in the study.

A flow diagram of the RCT protocol is presented in Fig. 1. The control group will have no intervention. During the 10-week intervention period participants in the control group healthcare center will be offered routine staff training opportunities. Participants in the intervention group will receive the intervention described below. The logic model used for the intervention planning and evaluation—the PRECEDE-PROCEED model—is illustrated in Fig. 2. Table 1 shows the key research questions and the data sources according to the model phases.

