### Data analysis

Descriptive and inferential statistical analyses will be conducted using IBM SPSS-Amos software. The Kolmogorov-Smirnov test will be correspondingly applied to check the normality of the data. If the data are normally distributed then t-tests, paired-samples t-tests, and analysis of variance (ANOVA) will be operated as needed. Analysis of covariance (ANCOVA) will be employed to investigate the difference in the mean scores of the experimental and control groups in terms of the study variables at the pre- and post-intervention stages. If the data are not normally distributed, non-parametric analysis will be used. In this case, the Mann-Whitney U test will be used to compare two groups before and after the intervention, and the Wilcoxon signed-rank test will be applied to compare each group at the pre- and post-intervention stages, and the Kruskal–Wallis test will be exploited for the between- and within-group comparisons.

In addition, structural equation modeling will be utilized to analyze and evaluate the fit of the model.

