## Discussion

The present study will be the first attempt to examine the effectiveness of an educational intervention, developed based on the SCT and integrated into the PRECEDE-PROCEED model, in improving resilience, social capital, PWB, and HPL among HCW. The ultimate goal of the study is present a workplace intervention that will boost resilience, social capital, PWB, and HPL for the benefit of employees and employers. This evidence-based study has several strengths, as we discuss below.

The extant literature includes several intervention studies to improve workplace health. Nevertheless, there are contradictory results. Whilst some interventions have confirmed the effectiveness of resilience training [43], other studies have considered it to be insignificant. The lack of consensus may be due to the quality of the intervention program, or the study settings or the statistical population involved in the study, or the measures used, or a combination of all of these. Workplace interventions to improve employee health and quality of life are complex. There is a need to use established theories and principles, as well as a health promotion/illness-prevention framework to support the essential risk assessment process [68], yet the literature suggests this is not so. This study is a theory-based intervention based on an established health promotion framework, using delivered using theory-based educational practices. This is a strength of this study.

This study will be an RCT—the most powerful tool in experimental research to investigate the effectiveness of an intervention [69, 70]. Conducting a randomized interventional study accordingly makes it possible to examine the effects of the intervention on the outcomes among individuals in experimental and control groups [71].

Another strength of this study is that the contents of the educational sessions will be delivered to the participants face-to-face [53] and using a variety of activities and media to support assimilation of the knowledge materials both during the sessions and as homework. This can help increase the learning of more contents during the education process [59, 60].

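### One healthcare center per arm: arm and center are the same variable, so individual-level tests cannot carry the RCT-strength conclusion that the protocol claims

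*Protocol article*

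**What the plan says.** In the protocol article, under Study design, setting and participants, "Recruitment will be from two large healthcare centers in the northern and southern parts of the city of Shiraz". Allocation is at center level: "The two healthcare centers will be randomly assigned to intervention and control settings following recruitment". The same section confirms that the control arm is a single center: "participants in the control group healthcare center will be offered routine staff training opportunities". The Abstract has the same one-site-per-arm structure but calls the sites cities: "healthcare workers of one city being given the educational intervention and the healthcare workers of the other city serving as a control group".

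The only chance element at worker level is the drawing of the sample from a staff list: "Thenceforth, the samples will be selected in a randomized manner". That is selection into the study, not allocation to an arm.

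The sample-size formula is for two independent means. It gives 66 per group, raised to 69 for 5% loss, and has no term for clustering. Under Data analysis, "If the data are normally distributed then t-tests, paired-samples t-tests, and analysis of variance (ANOVA) will be operated as needed"; ANCOVA is added for the comparison of the groups, and Mann-Whitney is the fallback if the data are not normal. None of these is described with a center or cluster term.

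On the design label, one sentence gives two answers: "This quasi-experimental study is a non-blinded randomized controlled trial (RCT". The Discussion takes the stronger one: "This study will be an RCT—the most powerful tool in experimental research to investigate the effectiveness of an intervention". The Conclusion again calls the study an RCT and vouches for its methodology. The limitations in the Discussion cover the missing pilot and the mix of job roles, but not the one-center-per-arm allocation.

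**The concern.** With one center in each arm, anything that changes at one center and not at the other during the study appears in the data as an intervention effect. Examples are a change of manager, a shift in workload or a local event. The Background section itself names manager communication and perceived justice as organizational influences on employees' mental health, so a center effect of exactly zero is not a safe premise.

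Two things are at stake. First, the planned tests take their standard errors from variation between workers within a center. That variation carries no information about how much two centers would differ without any intervention. Second, the article intends to take the program to other organizations if it is found effective, and to present that finding with the authority of an RCT. The design does not supply that authority.

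**Working it through.** **The plan's own figures.** The 66 cannot be reproduced, because the article gives the formula without values for alpha, power, standard deviation or difference. The step to 69 is consistent: 66 × 1.05 = 69.3 and 66 / 0.95 = 69.5 (70 if rounded up). Neither figure decides this point. What matters is that the formula has no clustering term.

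**Degrees of freedom.** Between-center degrees of freedom within arms = centers − arms = 2 − 2 = 0. Between-center variance cannot be estimated by any model, including one specified in an analysis plan that is not shown here.

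**Randomization distribution.** Two centers can be assigned in 2 ways. The smallest one-sided randomization p-value is 1/2 = 0.5; the smallest two-sided one is 2/2 = 1.0.

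**Effect on an individual-level test (illustration).** Inputs: m = 66 workers per center (from the article); two-sided 5% and the intracluster correlation ρ (both assumed). Total variance is set to 1.

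- True variance of the difference in means: 2 × [ρ + (1 − ρ)/m]
- Variance that the two-sample t-test uses: 2 × (1 − ρ)/m
- Ratio of true to assumed standard error: R = √[1 + mρ/(1 − ρ)]
- Type I error: two-sided tail of t with 2m − 2 = 130 degrees of freedom, beyond 1.978/R

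For ρ = 0.01: 66 × 0.01/0.99 = 0.667; R = √1.667 = 1.291; 1.978/1.291 = 1.532; two-sided tail = 12.8%.

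| ρ (assumed) | R (m = 66) | Type I error, m = 66 | Type I error, m = 69 |
|---|---|---|---|
| 0 | 1.000 | 5.0% | 5.0% |
| 0.005 | 1.154 | 8.9% | 9.1% |
| 0.01 | 1.291 | 12.8% | 13.1% |
| 0.02 | 1.532 | 19.9% | 20.5% |
| 0.05 | 2.115 | 35.1% | 36.0% |

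A simulation of 20,000 trials per setting with m = 66 gave 9.3%, 12.8%, 20.1% and 35.0% for the four non-zero values.

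**More workers do not help.** As m grows, the true variance tends to 2ρ, not to zero. At ρ = 0.01 the difference between two centers without any intervention has a standard deviation of √0.02 = 0.14 outcome standard deviations, however many workers are enrolled.

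**The case against.** Several points on the other side are fair.

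*The choice is deliberate.* Separate centers are used to prevent information passing between the groups, and the article says why these two were judged comparable. That is a legitimate reason for center-level allocation, and it stands. It does not justify individual-level error rates, and comparability is asserted without figures.

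*The centers are randomised.* They are, so it would be wrong to infer that the study has no random allocation. Over repeated assignments neither center is favoured. But a single assignment of two centers gives no measure of how far the observed difference may lie from the truth.

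*Both arms are measured at baseline.* The first hypothesis concerns change in mean scores, and ANCOVA on pre- and post-intervention scores is planned. Read as baseline adjustment, this reduces stable center differences such as staff mix or management style. This stands, and it limits the point: what clearly remains is differential change over the 10 weeks and the three-month follow-up. The relevant correlation is the residual one after adjustment, which may be smaller than the unadjusted one.

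*The sizes are assumed.* They are. A reader might infer that this trial's error rate is 13% to 35%. The documents do not support that: no intracluster correlation is given, and the table is for an unadjusted test. A reader might also infer a specific loss of power, but alpha, power and effect size are not stated either. Nor does social capital being a workplace concept show that the center-level correlation is high. It is measured by each worker's own report about colleagues and a supervisor, and may cluster more by workgroup than by center.

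*The article already says quasi-experimental.* It does, in the same sentence that says RCT, and the Discussion and Conclusion rely on the stronger label.

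**Conclusion.** The point holds. Complete overlap of arm and center, with 0 between-center degrees of freedom, follows from the stated allocation and depends on no assumed number. The individual-level p-values keep their nominal level only if the center-level correlation remaining after baseline adjustment is zero, and the data cannot show whether it is. The RCT-strength claims therefore attribute to the design a property that it does not have.

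The size of the error inflation is unknown. The range of about 9% to 35% illustrates an unadjusted t-test with 66 per center at assumed correlations of 0.005 to 0.05; it is not an estimate for the planned ANCOVA.

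Two stronger readings should be resisted. One is that any significant difference must be a center artefact: the design cannot separate the two explanations, which is not evidence for either. The other is that a result which stays significant after its standard error is inflated for some assumed correlation would establish effectiveness. It would not, because an assumed correlation does not separate the intervention from events at one center.

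**What to change.** Keep the two-center allocation and change the following:

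- In the Abstract, Study design, Discussion and Conclusion, use one label: a two-center quasi-experimental controlled before-after study with center-level allocation. Remove the RCT-strength claims, and let the Abstract refer to two centers rather than two cities.
- Under Data analysis, make the baseline-adjusted (ANCOVA) difference the reported comparison. Interpret it as a difference in change between these two centers, not as a causal effect of RCT strength.
- Add center confounding to the limitations in the Discussion, naming center-specific change during the program and follow-up.
- State beside the sample-size formula that 66 per group contains no allowance for clustering.
- Optionally, show the result with its standard error inflated over a range of assumed correlations, labelled as illustration and not used as a rule for claiming effectiveness.

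This needs wording changes and no additional participants. The price is that the stated strength of evidence becomes less favourable.

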### Demographic information

A researcher-made questionnaire will be used to collect information regarding participants sex, age, education level, marital status, and history of illness, seeking psychiatric support and taking medication. (Participants who report chronic illness needing medication, or consultations with a psychiatrist who give a positive answer at any of the three time points will be excluded from the study.)

*Social Capital at Work* [61]. This measure is made up of eight items that together assess the cognitive and structural components of social capital at work. Items explore mutual respect and trust between colleagues and a supervisor, reciprocity, participation in networks and collective action. An example is: “People feel understood and accepted by each other”. Answers to the statements are given using a five-point agreement scale where 1 = fully disagree, to 5 = fully agree, and low scores will indicate low social capital. This questionnaire has been reliably used in Iran [62].

*Resilience at Work Scale* [42]. The scale authors assert that resilience is a capability and that the scale supports intervention to support employees develop strengths in these areas to enable them to cope with work challenges. It comprises 20 items that assess seven aspects of resilience at work: living authentically (3 items), finding one’s calling (4 items), maintaining perspective (3 items), mastering stress (4 items), interacting cooperatively (2 items), staying healthy (2 items) and building networks (2 items). Each item is rated using seven-point agreement scale ranging from 1 = completely disagree to 7 = completely agree, and high scores indicate higher resilience. Previous studies have confirmed its reliability [39]. This will also be confirmed in this study through Cronbach’s alpha coefficient and test-retest method.

*Resilience Skills Questionnaire*. This is a 17-item researcher-made questionnaire based on three key constructs of SCT: self-efficacy, self-regulation and reinforcement from social support. Participants respond to each item using a 5-point agreement scale where 1 = strongly disagree, to 5 = strongly agree, and higher scores will indicate better status in each construct. A pilot study in a sample of the statistical population indicated the RSQ has good psychometric properties. This study will confirm its reliability through Cronbach’s alpha coefficient and test-retest method.

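### The 5% loss allowance behind 69 per group is not reconciled with the protocol's own rules for removing participants after enrolment

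*Protocol article*

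**What the plan says.** All references are to the protocol article.

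- **Sample size.** Under Study design, setting and participants: "The sample size is estimated to be 66 participants in each group". The Abstract (Methods) presents the same figure as a floor: "The minimum sample size required has been calculated as 66 individuals in each healthcare centers". The allowance follows: "Considering the 5% loss of observations, the final sample size will be determined to be 69 in each group". No basis for the 5% is given.
- **Removal for not taking part.** The exclusion criteria in the same section include "reluctance to continue the study/not participating in either intervention and/or surveys".
- **Removal for illness.** Under Demographic information, a further rule covers psychiatric consultations and medicated chronic illness: those "who give a positive answer at any of the three time points will be excluded from the study".
- **Attendance.** The Abstract says that people in the experimental arm "should participate in at least eight of the ten weekly educational sessions of the intervention and complete the surveys in the three stages".
- **Replacement.** It is described for one situation only, using the alphabetical list of staff: "If a person is not eligible, or does not give written informed consent, then they will be replaced with the next one available on the". Baseline data are collected after that step, and the two centers are allocated after recruitment.

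**The concern.** The allowance is described as a loss of observations, which reads as ordinary dropout. The removal rules go further, because they take out people who were properly enrolled and who may have returned every survey.

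The illness rule is also wider than the entry rule. Entry requires no self-reported history of severe illness, whereas removal is triggered by any chronic illness needing medication or by a psychiatric consultation. A person can therefore satisfy the first and be removed under the second. Removals at the two later surveys come after allocation, and nothing describes replacing them.

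Two things are at stake. The number analysed may fall below the stated minimum. In addition, some removals may be related to outcome: in a trial of resilience and psychological wellbeing, a psychiatric consultation during follow-up says something about how the participant is doing.

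**Working it through.** **Inputs from the document:** minimum 66 per group; loss allowance 5%; final 69 per group. No rate is given for non-participation, medicated chronic illness, psychiatric consultation, missed sessions or unreturned surveys.

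**Step 1: reproduce 69.**
- Dividing by the retained fraction: 66 / (1 − 0.05) = 69.47.
- Multiplying up: 66 × 1.05 = 69.30.
- Both give 69 to the nearest whole number and 70 when rounded up, so 69 is reproduced by rounding to nearest.

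**Step 2: what 69 allows.**
- Expected completers at 5% loss: 69 × 0.95 = 65.55, which is 0.45 of a participant below 66. With 70 it is 70 × 0.95 = 66.5.
- Room for loss: 69 − 66 = 3 people per group, and 3/69 = 4.3%. These three must cover withdrawal, missed surveys and every removal under the exclusion rules.

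**Step 3: sensitivity to the total loss.** The loss rates beyond 5% are assumed, because the document gives none. The article states no alpha, power, standard deviation or mean difference, so the power columns assume a two-sided alpha of 0.05, independent participants, and the standardised difference d that 66 per group would detect:

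d = √(2/66) × (1.960 + z for the planned power), which gives 0.488 for 80% and 0.564 for 90%.

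Power with n per group = Φ(d × √(n/2) − 1.960). The number to enrol is 66/(1 − loss), rounded up.

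| Total loss | Left of 69 | To enrol for 66 | Power if 80% planned | Power if 90% planned |
|---|---|---|---|---|
| 5% (stated) | 65.55 | 70 | 79.7% | 89.8% |
| 10% (assumed) | 62.1 | 74 | 77.6% | 88.2% |
| 15% (assumed) | 58.65 | 78 | 75.2% | 86.3% |
| 20% (assumed) | 55.2 | 83 | 72.6% | 84.2% |

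The table shows only how sensitive the plan is to the loss rate. It does not predict the loss and it does not verify the 66.

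**The case against.** The strongest reply is that no inconsistency can be computed without removal rates. Reluctance to continue and unreturned surveys are ordinary dropout, which a 5% allowance exists to cover. People whose illness is known at selection may be replaced from the list and so never reduce the 69. What clearly goes unreplaced is illness or consultation first reported at the two later surveys, which is a smaller group. Much of this stands. The document does not settle whether people who report illness on the baseline survey are replaced, and the 10% to 20% losses come from no part of it.

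Three stronger readings are tempting and are not supported:

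- A reader might infer that 5% is shown to be too low. It is unsupported and unreconciled, which is a weaker statement.
- A reader might infer that everyone attending fewer than eight sessions is removed. The Abstract says that they should attend eight; it does not say what follows if they do not. The exclusion criterion on non-participation sets no threshold. Attendance also concerns the experimental group only, so it could not add the same loss to both groups.
- A reader might infer that 69 came from multiplying by 1.05. Both calculations round to 69, so the figure cannot show which was used.

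The reply does not remove the core point. The article fixes a 5% allowance in one place and removals beyond missing data in two others, and it never relates them. Detail in a fuller document could explain the 5%, but the exclusion rules as published would still compete with it.

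**Conclusion.** The point holds as an unreconciled assumption. The 5% is not tied to the removals that the protocol itself prescribes, and no replacement is described for removals at the later surveys. The size is unknown because no rates are given. Under assumed total losses of 10%, 15% or 20%, about 62, 59 or 55 per group would remain against a minimum of 66. If 80% power was planned, it would fall to about 78%, 75% or 73% on the assumptions stated above.

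The difference between 69 and 70 is a separate remark of low severity. Strict rounding up of a minimum gives 70, but the shortfall of 0.45 of a participant costs only 0.2 to 0.3 percentage points of power (80% to 79.7%, or 90% to 89.8%).

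**What to change.** Define loss as missing outcome surveys only. Analyse all other enrolled participants in their allocated group, including those who attend few sessions and those who report illness or a psychiatric consultation after baseline. The 5% then covers only missing data. This means rewording the exclusion criteria under Study design, setting and participants and the exclusion sentence under Demographic information, and continuing to offer the surveys to these participants. It concerns who is surveyed and analysed, not who should continue with the sessions. It needs no extra participants, keeps precision, and avoids exclusions after allocation that may depend on outcome.

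If the removals are kept, give an expected rate with its basis, and restate either the expected evaluable number per group or the number to enrol.

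As a one-figure correction, state 70 per group (140 in total instead of 138), or keep 69 and say that about 65.6 completers per group are expected at 5% loss.
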